## Abstract

**Background::**

Type 2 Diabetes Mellitus (T2DM) is a chronic disease that is increasing the number of cases worldwide. The treatments currently used have not worked as expected. Alternative and complementary medicines were inserted in health services, especially in primary care, as an attempt to minimize risks and help control diseases such as diabetes. Among the herbal medicines used stands out cinnamon, which can serve as an adjuvant in the control of diabetes.

**Objective::**

To analyze the effectiveness of 3 grams of cinnamon (*Cinnamomum verum*) per day for 90 days in reducing glycemic and lipid levels in adults with T2DM compared with placebo

**Methods::**

A randomized, double-blind, placebo-controlled, phase II trial, which will be conducted at basic health units in the city of Parnaíba, state of Piauí, Brazil. In total, 130 people diagnosed with T2DM, followed at health units, with hemoglobin A1c > 6.5%, and using oral antidiabetic medicines, are expected to participate in the study. The intervention will last for 3 months, and each participant will receive a total of 3 bottles containing 120 capsules in each bottle of cinnamon or placebo. Each person should take 4 capsules daily, for 90 days. The patients will be distributed into the 2 groups by performing block randomization (n = 6) at a ratio of 1:1 according to a code generated by a software. Assessments of socioeconomic, clinical, lifestyle, anthropometric, and laboratory variables will be performed in 2 separate visits.

**Discussion::**

This study will be the first to investigate cinnamon to reduce glycemic, lipid, and anthropometric levels in Brazil. In case of favorable results, this therapy may be used as an alternative or additional medicine in cases where only oral antidiabetic agents are used and can promote the use of the product to minimize future complications of patients with diabetes and people who do not have the disease.

**Trial registration::**

RBR-2KKB6D, registered on December 11th, 2018.

## Introduction

1

Type 2 diabetes mellitus (T2DM) is a metabolic disorder known as a global health problem, characterized by elevated blood glucose levels. It is estimated that nearly 200 million people with diabetes are undiagnosed and; therefore, at greater risk of developing complications including kidney failure, blindness, amputations, heart disease, and stroke. These complications increase the cost of healthcare and decrease the quality of life.^[1]^

According to the International Diabetes Federation, the general target for glucose control in T2DM should be less than 7% of hemoglobin A1c (HbA1C) (53 mmol/mol).^[1]^ The T2DM management can prevent or reduce the risk of such complications. A 1% reduction in HbA1C is reported to be associated with a 21% lower risk of diabetes complications.^[2]^ Strategies to improve glycemic status are worth investigating. Losing weight, decreasing lipids, anthropometric indices, (eg, waist circumference) and body composition, along with lifestyle changes and drug therapy, are the main treatment for T2DM.^[3–5]^

However, due to the high prices of prescribed medications, polypharmacy, inadequate diet, the degree of dementia in some cases, low economic power, or even insufficient education, patients end up in clinical inertia.^[2]^

In this direction, in Brazil, the National Policy of Integrative and Complementary Practices was created in 2006,^[6]^ with the objective of implementing alternative treatments to evidence-based medicine in the Brazilian public health network, through the Unified Health System. The tendency of alternative and complementary therapies is increasing considerably, particularly herbal medicine, around the world.^[5]^ However, in many cases, there is insufficient evidence about its safety and efficacy.

Among the many herbal medicines examined so far,^[7–9]^ one deserves special mention for being useful in reducing both glycemic and lipid (and even anthropometric) biomarkers in patients with diabetes, which is the cinnamon.^[5]^ Despite encouraging results, the use of this product has not yet been investigated in countries such as Brazil, where the population has unique life characteristics, and where primary care health care has not been sufficient to manage diabetes patients with quality.

## Justification

2

The interest of this project is the evaluation of the efficacy of cinnamon to control the glycemic and lipid levels of people with T2DM. The justification for the importance of the proposal considers recent data from research conducted in Brazil. Among other information, it was revealed that the costs attributed to adult hospitalizations for diabetes were 19% higher than hospitalizations for other diseases. In addition, hospitalizations for cardiovascular diseases related to diabetes accounted for 45%.^[10]^ Certainly, this scenario is closely related to the quality of disease control and, therefore, requires, among others, the discovery of new adjuvant technologies for this control.

The implementation and applicability of the proposal is supported by the pillars of the Brazilian health system, and undoubtedly intends to promote its use as an adjuvant alternative in T2DM control, and may be made available by the Ministry of Health, aiming at reducing the economic expenses on health services. Also, this product may contribute to the minimization of pathogenesis-related adversities of high glycemic and lipid values in people who do not yet have chronic diseases. If cinnamon is effective in controlling T2DM, it will allow better resource allocations to manage this disease, producing health-promoting effects on costs and budgeting for other needs.

## Objectives

3

### General objective

3.1

To analyze the effectiveness of 3 grams of cinnamon (*Cinnamomum verum*) per day for 90 days in reducing glycemic and lipid levels in adults with T2DM compared with placebo.

### Specific objectives

3.2

(1)To investigate the efficacy of cinnamon in reducing the glycemic levels (HbA1C and fasting venous glucose) of people with T2DM compared with placebo;(2)To analyze the efficacy of cinnamon in lowering lipid levels (total cholesterol, low density lipid-cholesterol and triglycerides), and increasing high density lipid-cholesterol in people with T2DM compared with placebo;(3)To evaluate the efficacy of shin in reducing anthropometric values (weight, waist circumference, waist circumference, neck circumference, thigh circumference, hip circumference, body mass index, central adiposity index, neck-thigh ratio, waist ratio -quadrille, waist-to-thigh ratio, waist-to-height ratio) in people with T2DM compared with placebo.

## Methods

4

### Trial design

4.1

A randomized, double-blind, placebo-controlled, phase II trial, which will be conducted at Basic Health Units in the city of Parnaíba, state of Piauí, Brazil. In total, 130 people diagnosed with T2DM, followed at health units, and using oral antidiabetic medicines, are expected to participate in the study – according to sample calculations. This study complies with ethical guidelines in humans. The study was approved by the Research Ethics Committee of the State University of Piauí, under Opinion number 3.447.415, and was registered with the Brazilian Clinical Trials Network/World Health Organization Primary Registries under protocol RBR-2KKB6D.

For the purpose of greater transparency and quality of the research, Table 1 summarizes the enrolment, intervention, and assessment schedule, all of which are in accordance with the standard protocol items: recommendations for interventional trials recommendations.

**Table 1 T1:**
[figure not shown]
Schedule of enrolment, intervention, and assessment of treatments.

#### Baseline and post-intervention variables

4.1.1

##### Socioeconomic variables (baseline only)

4.1.1.1

Will be investigated: family economic income, years of study, marital status, type of work, skin color, gender, and so on.

##### Clinical questions

4.1.1.2

Will be investigated: how long the patient has diabetes, what medications the patient takes, if have some allergies, where the patients get the medicines, how often do the patients see the doctor, which professional does direct follow-up and patient health management, if they use alternative and complementary practices, if any herbal medicine is used for any clinical condition, etc. The blood pressure will be measured.

##### Lifestyle related variables

4.1.1.3

Will be investigated: If the patient uses alcohol, tobacco, if they do some physical activity and how often, how is the diet, and so on.

##### Anthropometric variables

4.1.1.4

Will be investigated: waist circumference, thigh circumference, neck circumference, abdominal circumference, hip circumference, height, weight, body mass index, central adiposity index, waist-hip ratio, neck-thigh ratio, and so on.

##### Laboratory tests

4.1.1.5

The tests will be collected: fasting glucose, HbA1C, total cholesterol, HDL, LDL, triglycerides, and the homeostatic model assessment of insulin resistance (HOMA-IR) index will be calculated.

#### Outcomes

4.1.2

##### Primary outcome

4.1.2.1

Reduction of glycemic levels (HbA1c and fasting venous glucose) after 3 months of use of the received capsules (cinnamon or placebo).

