##### Secondary outcome

4.1.2.2

After 3 months of use of the received capsules (cinnamon or placebo), the following secondary outcomes will be collected:

(1)Reduction of lipid levels (LDL cholesterol, triglycerides and total cholesterol);(2)Increase HDL cholesterol levels.(3)Reduction of anthropometric measurements (weight, waist circumference, waist circumference, neck circumference, thigh circumference, hip circumference, body mass index, central adiposity index, neck-thigh ratio, waist-hip ratio, waist-thigh ratio, waist-to-height ratio).

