### Sample size

4.3

The sample will be calculated based on a previous literature study.^[11]^ The sample size observed in the Vafa's^[11]^ study was calculated on the difference in HbA1C (%) for each person between the initial and final values, resulting in: {mean of differences in the cinnamon group – mean of differences in the control group} / {2 [((SD cinnamon group) 2 + (SD control group 2)/2]} = { –0.44 –(–0.10)}/{2 [(0.722 + 0.652)/2]} = 0.4957 ≅ 0.50. So, if we consider the effect of 0.50, we need 64 participants per group (128 total) for 80% power. Although we do not expect a large loss, if we assume a 20% loss, we will need to recruit about 162 participants to have 130 participants at the end of the study. The calculations were made in GPower 3.0 by choosing the *t* test for independent samples.

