### Statistical analysis

4.6

All variables will be analyzed descriptively, with numerical and visual summaries. The 2 groups will be compared to check for differences in socioeconomic and clinical variables between the 2 groups at baseline. Numerical variables will be analyzed using the *t* test and categorical variables will be analyzed using the chi-square test.

For HbA1c analysis (in%), the change in value from baseline to end of the study will be considered as the primary endpoint and the means of both groups will be compared using the *t* test for independent groups. The significance level for this test will be 0.05. The analysis will follow the intention-to-treat principle, that is, the participant is analyzed in the group to which he was assigned, regardless of completing treatment as prescribed.

Secondary analyses will include means tests (*t* test) for numerical secondary variables, proportional tests for binary secondary variables, and chi-square test for categorical variables with more than 2 categories. Although we continue to use the significance level of 0.05, these tests will be interpreted with caution as the study was not designed to have statistical power for all of these tests. These tests will be considered exploratory.

Depending on the outcome of the primary outcome, exploratory analyzes will incorporate socioeconomic and clinical variables using regression analysis, where the final HbA1c value at the end of the study is the response variable, and the initial value, socioeconomic, and clinical variables, and the group of treatment will be the explanatory variables. Before statistical analysis, we will evaluate the amount and type of missing values. If necessary and possible, we will use multiple imputations to analyze the data. However, we will also perform the analysis with the full data and the final reports will contain the various analyzes so that the reader can compare them (sensitivity analysis).

Statistical analyses will be performed on SPSS version 25 (SPSS Inc., Chicago, IL) and Stata/SE 15.0 (Stata Corporation, College Station, TX) software for data analysis. Graphics will be done in R Studio.

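### The outcome section makes fasting glucose primary alongside HbA1c, but the sample size and the primary test use HbA1c alone; the sections must be reconciled

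*Protocol article*

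**What the plan says.** Four sections of the protocol article bear on the role of fasting glucose.

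- Section 4.1.2.1 (Primary outcome): "Reduction of glycemic levels (HbA1c and fasting venous glucose) after 3 months of use of the received capsules (cinnamon or placebo". HbA1c and fasting glucose stand side by side, with no order between them.
- Section 4.1.2.2 (Secondary outcome): the list opens with "Reduction of lipid levels (LDL cholesterol, triglycerides and total cholesterol" and continues with HDL cholesterol and anthropometric measures. Fasting glucose is not on it.
- Section 4.3 (Sample size): the effect comes from an earlier study and was "calculated on the difference in HbA1C (%) for each person between the initial and final values". Glucose does not enter.
- Section 4.6 (Statistical analysis): "For HbA1c analysis (in%), the change in value from baseline to end of the study will be considered as the primary endpoint". The two group means are compared with an independent-groups t test, and "The significance level for this test will be 0.05". Secondary variables are also tested at 0.05, but "These tests will be considered exploratory". Fasting glucose is not mentioned by name.

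**The concern.** Fasting glucose is primary where outcomes are defined and has no primary role where the trial is sized and analysed. Since it is also missing from the secondary list, its exploratory status under section 4.6 can only be inferred by elimination.

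This matters most if the two measures disagree. Suppose fasting glucose falls clearly and HbA1c does not. Under section 4.1.2.1 the report could claim success on a primary outcome. Under section 4.6 the primary endpoint has failed and the glucose result is at most an exploratory signal. The choice between these readings would be open after the data are seen. Section 4.6 also makes its follow-on regression analyses depend on how the primary outcome turns out, and with two discordant primaries that trigger is unclear.

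**Working it through.** **Inputs from section 4.3.** Mean HbA1c changes −0.44 (cinnamon) and −0.10 (control); SDs 0.72 and 0.65 (the squares and the root sign appear to have been lost in the printed formula); 80% power; 64 per group; 20% loss. **From section 4.6:** significance level 0.05. Sidedness is not stated; two-sided is assumed because it reproduces the 64.

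**Step 1: reproduce the plan's figure.**

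- d = (0.44 − 0.10) / √[(0.72² + 0.65²)/2] = 0.34 / √[(0.5184 + 0.4225)/2] = 0.34 / 0.6859 = 0.4957, rounded in the plan to 0.50.
- Two-sided t test at 0.05 with d = 0.50 (noncentral t): 64 per group, power 80.1%. With d = 0.4957 unrounded, 64 per group gives 79.5%.
- Loss: 130 / 0.8 = 162.5, against about 162 stated.

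With HbA1c change as the only primary endpoint, the 5% error rate and the roughly 80% power both hold.

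**Step 2: what follows if both measures are primary.** The document gives no correlation between the two test statistics and no effect or SD for glucose. The correlation r is therefore varied from 0 to 0.9, and d = 0.50 is assumed for glucose where power is needed. The calculation uses a bivariate normal with critical value 1.96.

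- *Either may succeed, each at 0.05.* Familywise error = 1 − P(|Z1| < 1.96 and |Z2| < 1.96). At r = 0 this is 1 − 0.95² = 9.75%.
- *Both must succeed.* Each statistic has mean 0.50 × √(64/2) = 2.83. Power = P(Z1 > 1.96 and Z2 > 1.96). At r = 0 this is Φ(2.83 − 1.96)² ≈ 0.807² ≈ 65%.

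| r | Familywise error, either rule | Power at 64 per group, both rule | n per group for 80%, both rule |
|---|---|---|---|
| 0 | 9.75% | 65% | 83 |
| 0.5 | 9.1% | 70% | 79 |
| 0.8 | 7.8% | 74% | 74 |
| 0.9 | 7.0% | 76% | 71 |

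The error figures count false positives in either direction. Counting only those that favour cinnamon, they are 4.9% (r = 0) to 3.5% (r = 0.9), against 2.5% for one two-sided test.

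**Step 3: the cost of keeping two primaries under an either rule.** With 0.025 for each (Bonferroni) and d = 0.50, power per measure at 64 per group is 71.2%. Restoring 80% takes 78 per group, 156 in total, or 156 / 0.8 = 195 recruited.

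**The case against.** The strongest reply is that section 4.6 settles the matter. It speaks of one primary endpoint, gives it one test and one significance level, and agrees with section 4.3. The follow-on regression also has final HbA1c as its response. Every section that does statistical work points to HbA1c, and the only confirmatory test written down is for HbA1c. This stands, and it limits the consequence. A reader might infer that the trial has no success rule at all, or that its 5% error rate or 80% power is already lost. The document does not support that: section 4.6 states a rule, and under it both figures hold.

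A second reply is that a rule for combining two primaries may sit in a statistical analysis plan or full protocol that is not shown. That also stands, so the absence of such a rule is not the fault here. Third, the figures in step 2 describe rules that the document never states and rest on assumed inputs; they illustrate what is at stake if section 4.1.2.1 is taken at its word.

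The contradiction itself survives. Section 4.6 neither mentions fasting glucose nor withdraws section 4.1.2.1, and readers take the primary outcome from the section that bears that title.

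**Conclusion.** The point holds as a contradiction about the status of fasting glucose: primary in section 4.1.2.1, outside the primary endpoint in sections 4.3 and 4.6, and absent from the list in 4.1.2.2. As analysed under section 4.6, the trial keeps its error rate and its planned power. Only if section 4.1.2.1 governs is there a loss, and it takes one form or the other: an inflated error rate if either measure suffices, or reduced power if both are required. The two do not occur together. The error range rests on the assumed correlation; the power range rests on that and on the assumed glucose effect. It is worth correcting before analysis, because as written it leaves open which result counts as primary.

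**What to change.** In section 4.1.2.1, state one primary outcome: change in HbA1c (%) from baseline to the end of the 3-month intervention. Add fasting venous glucose to the secondary outcomes in section 4.1.2.2, where the exploratory status given in section 4.6 will then plainly apply to it. Section 3.2 needs no edit, since its objectives are not ranked and may name both measures.

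This matches the sample size and the analysis already written, so the number of participants, the test and the significance level are unchanged. The price is that fasting glucose loses primary status. If the sponsor wishes to keep both as primary, the success rule has to be stated and the trial re-sized: about 78 per group with a Bonferroni split, or about 71 to 83 per group if both must succeed, under the assumptions above.

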##### Secondary outcome

4.1.2.2

After 3 months of use of the received capsules (cinnamon or placebo), the following secondary outcomes will be collected:

(1)Reduction of lipid levels (LDL cholesterol, triglycerides and total cholesterol);(2)Increase HDL cholesterol levels.(3)Reduction of anthropometric measurements (weight, waist circumference, waist circumference, neck circumference, thigh circumference, hip circumference, body mass index, central adiposity index, neck-thigh ratio, waist-hip ratio, waist-thigh ratio, waist-to-height ratio).

### Participants

4.2

People diagnosed with T2DM, from Parnaíba city, possibly eligible to participate in the study. Recruitment will be based on the list of people with T2DM, registered and followed up at each Health Unit. Recruitment will be at least 10 days before the start of data collection. Recruitment will be carried out by community health workers from each health unit.

#### Inclusion criteria

4.2.1

(1)Men or women aged 18 to 80 at Visit #1;(2)Having a diagnosis of T2DM, confirmed for at least 5 years;(3)On oral antidiabetic drugs;(4)HbA1C > 6.5% (Tests performed before the subjects entered the research);(5)Preserve cognitive functions, according to the Mental State Mini-Exam.

#### Exclusion criteria

4.2.2

(1)Patients with cinnamon allergy;(2)Patients using cinnamon or another herbal medicine for diabetes treatment;(3)Patients diagnosed with alcoholic liver disease, cirrhosis or abnormal basal liver function;(4)Patients on insulin therapy;(5)Women who are breastfeeding, pregnant or taking contraceptives;(6)Patients with heart, liver or respiratory failure;(7)Patients with bleeding disorders who are taking coumarin derivatives (eg warfarin).

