#### Discontinuing criteria

4.2.3

(1)A participant wishing to withdraw from the study for any reason;(2)Serious adverse events or unusual changes in laboratory tests;(3)Patients taking another type of herbal medicine during this study.

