#### Blinding

4.5.2

Due to the objectives of the study, the identity of the test and control treatments will not be known to the principal investigator, data collection team, laboratory analysis laboratory, or patients. The following study procedures will be applied to ensure the triple concealment of study treatments.

(1)Access to the randomization list will be strictly controlled;(2)The capsules, packaging, and labeling of test and control treatments will be identical to maintain confidentiality about the type of treatment;(3)The concentrations of cinnamon or placebo in each capsule will be the same to minimize the breach of treatment confidentiality.

The treatment received by each person will be revealed after the completion of the clinical intervention and after the study database has been completed.

During the study, blinding can only be broken in emergencies when knowledge of the patient's treatment group is necessary for patient management. When possible, the investigator should discuss the emergency with the attending physician before revealing which group the patient is in.

Participants will be disengaged from study medication if necessary, for their safety or if the participant needs emergency surgery and information is requested on all treatment interventions. This is expected to occur very rarely, or never. Only in the event of an emergency where the participant cannot be adequately treated without knowing the identity of the study medication will this be revealed.

In an emergency, the primary care physician where the patient is being followed or the treating physician will be informed if the patient is receiving cinnamon or placebo. If there is no problem with this, the study will move on.

If it is really necessary to “break” the blinding, then the study coordinator/supervisor will contact the study team members responsible for the confidentiality of the randomization information to retrieve the sealed document.

A protocol bypass form must be completed for any event that requires unraveling the participant's assignment.

In the event of blinding “breakage”, the following information will be recorded:

(1)The identification of the participant;(2)The reason for the “break”;(3)The member of the study responsible for the breakage of blinding;(4)A list of people who are no longer blind to the treatment of the person concerned.

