#### Monitoring and security

4.5.3

Information on all serious adverse events, adverse events, recruitment, and retention, data integrity and data quality will be available for review by designated research group members. Interim safety analyses will be performed periodically throughout the study. While participant safety is the primary concern of the study, it is difficult to formulate precise discontinuity or interruption guidelines that cover all possible situations that may arise.

Adverse events, particularly severe ones, will need to be carefully considered by the research group regarding treatment group imbalances. There are no safety concerns expected with the drugs administered in this study. Cinnamon has been studied not only by the research group, but by other researchers around the world, so there is no reason to believe that its safety and tolerability are a significant problem. In addition, the group will analyze safety data and ensure the scientific validity and ongoing merit of the study.

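### Exclusion criterion 5 bars women taking contraceptives and asks for no other protection, so among women who could become pregnant it removes users of contraceptive drugs and admits those using no method

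*Protocol article*

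**What the plan says.** Three parts of the protocol article decide which women can enter.

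- **Inclusion criteria (4.2.1).** Item 1 admits "Men or women aged 18 to 80 at Visit #1". Item 2 requires "Having a diagnosis of T2DM, confirmed for at least 5 years". Neither these nor the other inclusion items mention menopause, sterilisation or contraception.
- **Exclusion criteria (4.2.2).** Item 5 bars "Women who are breastfeeding, pregnant or taking contraceptives". This is the only rule on contraception in the article, and no reason is given for it.
- **Interventions and procedures (4.5).** Participants take cinnamon or placebo capsules daily for 90 days.

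Three further places bear on the point. Discontinuing criteria (4.2.3) lists voluntary withdrawal, "Serious adverse events or unusual changes in laboratory tests", and use of another herbal medicine; pregnancy is not named. Blinding (4.5.2) states: "Participants will be disengaged from study medication if necessary, for their safety". Monitoring and security (4.5.3) states: "There are no safety concerns expected with the drugs administered in this study".

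**The concern.** One line excludes pregnancy and, alongside it, the women who are taking drugs to avoid pregnancy. It sets no replacement condition. Among women who could become pregnant, the rule therefore selects against one protected subgroup and leaves entry open to the unprotected one.

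What is at stake is participant safety. The sponsor keeps pregnant women out at entry, so it is consistent with the sponsor's own criteria to avoid pregnancies that begin while capsules are being taken. There is a lesser measurement aspect. A woman who conceives during the study would be in an excluded state by the final visit, where the secondary outcomes include "Reduction of anthropometric measurements (weight, waist circumference" and other body measurements. The statistical inference is not at stake.

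**Working it through.** **Step 1: apply the criteria as printed.** Take women who could become pregnant, who meet every other criterion, and who are neither pregnant nor breastfeeding.

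| Woman's situation | Under item 5 |
|---|---|
| Takes a contraceptive drug | Excluded |
| Uses a barrier method or non-hormonal device | Not expressly barred; method not required |
| Uses no method | Admitted |

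A sterilised woman is also admitted, but sterilisation is not required. Nothing elsewhere in the article changes these results. The safety provision in 4.5.2 can act only once a pregnancy is known, so it does not prevent one.

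**Step 2: test the rule against its two possible purposes.**

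- *Safety.* If pregnancy is excluded to protect mother and fetus, the rule works in the wrong direction: it removes women protected by drugs and admits women with no protection.
- *Metabolic confounding.* If all three states are excluded because they may shift glucose, lipids or weight, keeping hormonal products out is defensible. The line should then name hormonal products, and it still lets an unprotected woman move into another excluded state, pregnancy, before the final measurements.

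Both purposes call for a condition on other methods.

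**Step 3: size.** The article gives no figure, so every input except two is an assumption. Those two are the recruitment target of 162 (Sample size, 4.3) and the 90 days of capsules.

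- Number who could become pregnant: n = 162 × proportion women × proportion of these who could become pregnant.
- 90-day chance of pregnancy per woman: q = 1 − (1 − p)^(90/365), where p is an assumed 12-month chance averaged over women using non-drug methods and women using none.
- Expected pregnancies: n × q. Chance of at least one: 1 − (1 − q)^n.
- Cinnamon arm: replace n by n/2, because allocation is 1:1 (Randomization, 4.4).

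| | Low | Middle | High |
|---|---|---|---|
| Proportion women (assumed) | 50% | 60% | 70% |
| Proportion who could become pregnant (assumed) | 2% | 5% | 10% |
| n | 1.6 | 4.9 | 11.3 |
| Share of 162 | 1% | 3% | 7% |
| p (assumed) | 3% | 10% | 20% |
| q | 0.75% | 2.56% | 5.35% |
| Expected pregnancies, both arms | 0.01 | 0.12 | 0.61 |
| At least one, both arms | 1% | 12% | 46% |
| Expected pregnancies, cinnamon arm | 0.006 | 0.06 | 0.30 |
| At least one, cinnamon arm | 0.6% | 6% | 27% |

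The high column stacks three upper values and should not be read as likely. If an effective method cut q by an assumed 90%, the chance of at least one pregnancy across both arms would fall to about 0.1%, 1% and 6%.

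**The case against.** The strongest reply has four parts.

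1. *This is an omission, and a journal article may leave contraception detail to the full protocol.* This stands in part. The absence of a pregnancy test from Laboratory tests (4.1.1.5), or of a pregnancy-handling procedure, is not held against the plan. But the article does print a contraception rule, and that rule already decides who enters. A fuller document could add safeguards, yet the printed criterion would still need a qualifier.

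2. *The three states share a metabolic rationale, and 4.5.3 expects no safety concerns.* This is plausible, and it is why excluding hormonal products should remain open to the sponsor. It does not explain why unprotected women are admitted without any condition.

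3. *The word 'taking' most naturally means drugs.* Accepted. A reader might infer that only unprotected women can enter, or that the trial forbids contraception altogether. The text does not support either reading: barrier methods, non-hormonal devices and sterilisation are not barred, and some of the women admitted will rely on them.

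4. *The numbers are small and assumed, and half the women take microcrystalline cellulose.* Accepted, and the cinnamon-arm rows above reflect it. The participant contacts in 4.5, weekly retention calls and fortnightly follow-up calls, could also bring a pregnancy to light. They are contacts during treatment and do not amount to prevention at entry.

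A reader might also infer harm to the trial's results. The documents do not support that. A pregnancy begun after entry would be less than 90 days old at the final measurement, and the secondary tests are declared exploratory (Statistical analysis, 4.6). With 0.12 pregnancies expected in the middle case, no group mean would move noticeably.

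**Conclusion.** The point holds as a minor participant-safety correction. As worded, item 5 removes women on contraceptive drugs, admits women using no method, and requires no alternative during 90 days of capsules. That conclusion rests on the text alone.

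The size is uncertain and probably small. The 5-year diagnosis requirement narrows the group, though with entry from age 18 the criteria do not make it empty. The figures of about 2, 5 or 11 women, and of 0.01, 0.12 or 0.61 expected pregnancies, depend wholly on the assumptions shown. Sample size, power, type I error and the primary HbA1c comparison are unchanged.

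**What to change.** Reword item 5 of 4.2.2 along these lines: *Women who are pregnant or breastfeeding; women taking hormonal contraceptives; and women who could become pregnant, unless at entry they use an effective non-hormonal method (sterilisation counts) and agree to continue it to day 90.* Current use and agreement can both be established at entry, whereas actual use to day 90 cannot. If the sponsor does not regard hormonal products as a metabolic concern, drop the second clause and accept them as an effective method.

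The cost is one edited line. Women who could become pregnant and use no effective method become ineligible. Under the assumptions above that is at most about 2, 5 or 11 of 162, to be replaced from the health-unit lists. Keeping the hormonal exclusion avoids any added variance in the lipid outcomes; allowing stable hormonal users may add some.
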